#### Sensitivity and comparator analyses

The cancer registry does not collect data on BMI, CCI, or history of previous surgery for non-malignant indications. Given that we will be unable to emulate these potential factors, residual confounding arising from these factors is a major limitation of this study. Thus, we will perform sensitivity analyses.Of residual confounding using the E-value method (VanderWeele and Ding 2017) to provide a quantitative bias analysis for potential residual confounders (BMI, comorbidity, and previous abdominal surgery for non-malignant indications), and.After excluding patients with missing data to further evaluate the potential for selection bias that would otherwise have occurred if such cases were excluded. Further sensitivity analysis will be performed by including all patients with advanced local disease (stage T4N0-2M0).

In addition, a comparative analysis of the same but unemulated study population that started treatment at any point in time will be performed via classical Cox regression to assess the influence of our emulation process. As identified by the DAGs, the treatment effect, which adjusts for “age, grade, performance status, and tumor laterality” in this comparative model will be unbiased. Through this, we will practically examine whether the conclusion of the comparative analysis actually differs from that of the emulated study (see Additional file 2). Another comparative analysis of the same emulated population will be performed via the inverse-probability weighted regression adjustment (doubly robust) method. This approach combines the outcome modeling strategy of regression adjustment and the treatment modeling strategy of inverse-probability weighting (Smith et al. 2022). It is referred to as “doubly robust” because although it requires running two models, of which only one—the treatment or outcome model—needs to be correctly specified to obtain an unbiased estimate of the treatment effect (Smith et al. 2022).

All our analyses will be performed in STATA (version 18.0, College Station, TX: StataCorp LLC), and statistically significant associations will be declared at a p-value of less than 0.05.

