Follow-up	Follow up begins at diagnosis and the random allocation of patients to either treatment arms and then scheduled follow-up information according to German S3- guideline for colorectal cancer (German Guideline Program in Oncology 2019).	Patients will be followed from time-zero (date of diagnosis) until death from any cause, last date of information or administrative censor date (31.12.2023), whichever will come first.
Censoring	Loss to follow-up, administrative censor date (31.12.2023).	Same as target trial
Causal contrast	Intention-to-treat effect, per-protocol	Observational analogue of the per-protocol effect
Effect measure	Hazard ratio (HR), mean survival time difference	Same as target trial
Analysis plan	Multivariable Cox regression, absolute risk difference and restricted mean survival time (RMST)	Inverse-probability weighted Royston- Parmar parametric survival model. Further to the HR, absolute risk-difference, RMST difference will be calculated.
Covariate adjustments	ϖ Socio-economic characteristics: Age at colon cancer diagnosis (in years) and sex. ϖ Clinical characteristics: UICC^b^ stage (I, II or III), treating institutions, tumor laterality (left or right), treatment period (2008–2009, 2010–2014, 2015–2018), performance score (ECOG = 0, 1, or 2), hospital classification (certified colon center or not), local residual tumor margin status (yes, no, or not assessable), grade (low, intermediate or high), and number of harvested lymph nodes (< 21 or ≥ 21).	ϖ Socio-economic characteristics: same as target trial. ϖ Clinical characteristics: same as target trial.
Sensitivity analysis	Excluding cases with missing values (complete case analysis, CCA)	Sensitivity analyses: - 1) Repeat the same analysis on patients with complete case data - 2) Including all advanced local disease (stage T4N0-2M0) cases - 3) Quantitative bias analysis using the E-value method to evaluate the effect of potential residual confounders (BMI, comorbidity, previous abdominal surgery for non-malignant indications)
Comparator analysis		Comparator analyses: - Comparator 1) DAGs-guided naïve analysis of using fully adjusted cox proportional hazards model - Comparator 2) An Inverse-probability-weighted regression-adjustment (Doubly robust) analysis

^a^ ICD-10 = The International Classification of Diseases, 10th Revision

^b^ UICC = Union for International Cancer Control

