In the web-based DAGitty environment (https://www.dagitty.net/), we will utilize directed acyclic graphs (DAGs) to determine the minimum necessary adjustment sets of confounders to control for within the comparative multivariable model. This approach mitigates the risk of bias that may arise from conditioning on intermediate covariates or colliders and mediators (Textor et al. 2011; Tonnies et al. 2022). The causal diagram for the comparative multivariable Cox model is complemented by a literature review and discussion to identify confounders, colliders, mediators and prognostic factors (Austin and Stuart 2015; Lederer et al. 2019). By adjusting the minimum sufficient adjustment sets of confounders in our comparative model, we will be able to block any backdoor bias paths (remove relevant confounding) when estimating the total causal effect of surgical treatment modality on all-cause mortality.

We will consider the following baseline characteristics (measured before or at time-zero) as potential confounders: Age at colon cancer diagnosis, sex, year of surgical treatment (classified according to the implementation and update series of the German S3- guideline for colorectal cancer (German Guideline Program in Oncology 2019) as 2008–2009 [pre-implementation], 2010–2014 [first update], or 2015–2018 [second update]), tumor laterality (right-sided [caecum and ascending colon] tumor or left-sided [descending and sigmoid colon] tumor), hospital type (classified as either a registered colorectal cancer center or other group), performance status (ECOG ≤ 2 or Karnofsky performance status score ≥ 50%), and histologic grade (low, intermediate or high), UICC stage (I, II or III), and local tumor size (T-stage). In addition, we will adjust the following two variables that serve as quality indicators of performed surgical procedure: minimum number of harvested lymph nodes (classified as < 21 or ≥ 21) (Choi et al. 2010), and local residual tumor status within 3 months of diagnosis (no (R0), yes (R1 + R2), not assessable or missing). We will also extract the following dates accurate to the month (date of birth, diagnosis, surgery, death, neo/adjuvant therapy initiation, and conversion to open surgery) and other covariates (project specific pseudonym, tumor IDs, cause of death).

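### The Cox comparator is called unbiased despite acknowledged unmeasured confounding, and because its population and covariates differ from the emulation's, it cannot by itself attribute a difference to the emulation

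*Protocol article*

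**What the plan says.** Under Sensitivity and comparator analyses, the protocol article announces "a comparative analysis of the same but unemulated study population that started treatment at any point in time". This analysis "will be performed via classical Cox regression to assess the influence of our emulation process". The adjustment set, attributed to the DAGs, is "age, grade, performance status, and tumor laterality", and the treatment effect "in this comparative model will be unbiased".

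The paragraph before, in the same section, says of BMI, the Charlson index and previous surgery for non-malignant indications that "residual confounding arising from these factors is a major limitation of this study".

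Table 1 (Comparator analysis row) describes the same model as a DAG-guided naïve analysis "using fully adjusted cox proportional hazards model".

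The Statistical analysis section says the DAG serves to find a minimal adjustment set for this comparator. It then introduces a longer list: "We will consider the following baseline characteristics (measured before or at time-zero) as potential confounders".

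Table 1 (Eligibility row, emulated trial) makes laparoscopic or open colectomy within 90 days of diagnosis an entry condition.

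**The concern.** Two things look wrong.

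- **The claim.** A model that lacks three variables the authors regard as a major source of residual confounding is said to give an unbiased effect.
- **The contrast.** The model is offered as a way to see what the emulation contributes, and the population is called the same. Yet the population, the covariates and the design all change between the two analyses.

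At stake is how the comparison will be read. If the two hazard ratios agree, the label unbiased lends the agreement more weight than it can bear. If they differ, the difference may be put down to cloning, censoring and weighting when it could come from late-operated patients or from the covariates left out.

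**Working it through.** The protocol states no sample size, event count or expected effect for this comparison, so there is no planned figure to reproduce. The check sets its statements side by side.

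**1. The claim of no bias.** The sentence is tied to the DAGs, so it is not wholly without condition. A DAG can justify a choice among measured covariates. It cannot supply BMI, comorbidity or previous surgery, which the registry does not hold. If these are confounders of the emulated estimate, as the protocol says, they confound the Cox estimate as well.

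**2. The population.**

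| | Time from diagnosis to surgery |
|---|---|
| Emulation (Table 1, Eligibility) | within 90 days |
| Cox comparator (Sensitivity and comparator analyses) | any time |

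Patients operated on after 90 days enter only the Cox model. Their number is not given, so this part cannot be sized.

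**3. The covariates.**

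- Cox comparator: age, grade, performance status, laterality = 4.
- Baseline confounders listed under Statistical analysis: age, sex, treatment period, laterality, hospital type, performance status, grade, UICC stage, T-stage = 9.
- Not in the Cox model: 9 - 4 = 5 (sex, treatment period, hospital type, UICC stage, T-stage).
- The section adds two surgical quality indicators, lymph nodes harvested and residual tumour status, making 11. These follow treatment, so leaving them out of a total-effect model is no fault and they are not counted here.
- The Table 1 list is similar: it has treating institution and no T-stage.

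The protocol does not state outright which covariates enter the weight models. I take it to be these lists.

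Elsewhere the protocol treats several of the five as important. Under Design of the target trial and the emulated trial, randomisation in the target trial is stratified by stage and hospital, and period-specific analyses are planned to limit bias from changes in practice.

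**4. What an omitted covariate could do (assumed inputs only).** Suppose the true HR is 1 and one binary confounder with hazard ratio h is omitted. Let its prevalence be p_L (laparoscopic) and p_O (open). To a rare-event approximation:

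apparent HR = [1 + (h - 1) p_L] / [1 + (h - 1) p_O]

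- h = 1.5, p_L = 0.30, p_O = 0.35: 1.15 / 1.175 = 0.98
- h = 2.0, p_L = 0.30, p_O = 0.40: 1.30 / 1.40 = 0.93
- h = 3.0, p_L = 0.30, p_O = 0.50: 1.60 / 2.00 = 0.80

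None of these inputs comes from the protocol. The direction follows from assuming a higher prevalence in the open group. The formula also ignores any control gained through the four covariates kept. It shows only that the adjustment set can move the HR with no contribution from the emulation.

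**5. The other comparator.** The doubly robust analysis keeps the emulated population. It does not remove the emulation, so it does not isolate its influence either.

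**The case against.** The strongest defence is that the claim refers to a DAG in a supplementary file that is not shown. A minimal sufficient set is normally shorter than a list of candidate confounders, and fully adjusted may mean adjusted for that set. This stands: four covariates against nine is not in itself a contradiction, although a reader might infer one. It does not rescue the word unbiased, because no DAG set can include what was not recorded.

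Second, the 90-day window can be seen as part of the emulation, since the grace period appears only in the emulated-trial column of Table 1. That is arguable. But 90 days is also an eligibility criterion, so the two populations are not the same.

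Third, the protocol also gives a more modest aim, to see whether the conclusions differ, and the planned model can answer that. This stands too. The comparison is usable as description; what it lacks is attribution.

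A reader might also infer that the Cox model suffers from immortal-time bias. The documents do not show this. The study population consists of operated patients in both groups, the comparator's time zero is not stated, and nothing indicates that time to surgery differs between the groups.

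Nor do the documents support a figure in percentage points for the bias from omitting stage or period. They give no stage mix, laparoscopy uptake or mortality by group.

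**Conclusion.** The point holds in a limited form. The claim that the four-covariate Cox effect will be unbiased conflicts with the residual confounding admitted in the same section. The comparator differs from the emulation in population and covariates as well as in design, so neither a difference nor an agreement can by itself be attributed to the emulation.

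The size is unknown. What can be counted is five pre-treatment covariates absent from the Cox model and an unstated number of late-operated patients. The conclusion assumes that the weight models use the listed covariates. It does not depend on the illustrative hazard ratios.

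This is a secondary analysis, and the primary weighted estimate does not rest on it. It merits correction because the protocol uses it to judge its own method.

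**What to change.** 1. Add a Cox comparator on the same patients as the emulation (surgery within 90 days), with the same pre-treatment confounders as the weight models, including UICC stage, T-stage, treatment period, hospital type and sex. If the weight models also carry the two surgical quality indicators, say so, because the two analyses would still differ by them.
2. Keep the any-time, DAG-minimal model as an extra row.
3. State that the comparator is unbiased only if the DAG is correct and there is no unmeasured confounding.
4. Reconcile the DAG set with the confounder list under Statistical analysis, giving the reason each listed variable drops out, and with the naïve and fully adjusted labels in Table 1.
5. Preferably compare the analyses on standardised 5-year risk or RMST differences, since a covariate-conditional HR and a weighted HR are not the same quantity.

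The cost is one more Cox model, the standardisation if adopted, and revised wording. No new data are needed.

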## Discussion

This study aims to causally evaluate the effect of laparoscopic versus open colectomy on 5-year OS by applying a target trial emulation methodology with a clone-censor-weight approach. Our study will be based on data from the Mecklenburg-Western Pomerania Cancer Registry, focusing on patients diagnosed with stage I – III colon cancer between 2008 and 2018. Disease stage- and treatment-period specific results will also be provided. A limitation of this study is potential residual confounding due to missing BMI, comorbidity and previous abdominal surgery data in the registry. To address this, a quantitative bias analysis using the E-method will be conducted. The analysis will increase robustness by reducing biases commonly found in observational studies (Emilsson et al. 2018; Hernan et al. 2016). This enriches the existing evidence from population-based data and contributes to a better understanding of the causal impact of surgical modalities on the long-term survival of patients with colon cancer. The application of such novel causal analysis approaches may further increase the utility of big administrative databases for answering pressing clinical questions (Hernan and Robins 2016).

## Conclusions

The results of this study will substantiate existing evidence on the comparative effectiveness of laparoscopic versus open colectomy in patients with stage I–III colon cancer. This may guide clinical decisions as to whether a laparoscopic approach is as safe as an open approach in terms of improving 5 year overall survival in these patient groups.

## Data Availability

No datasets were generated or analysed during the current study.

## Abbreviations

ASIR: Age-standardized Incidence Rate
BMI: Body Mass Index
CCI: Charlson Comorbidity Index
CERBOT: Comparative Effectiveness Research Based on Observational Data to Emulate a Target Trial
DAGS: Directed Acyclic Graphs
ECOG: Eastern Cooperative Oncology Group
GRADE: Grading of Recommendations Assessment, Development and Evaluation
GIST: Gastrointestinal Stromal Tumor (GIST)
ICD-10: The International Classification of Diseases, 10th Revision
KFRG: Cancer Early Detection and Registry Act (Krebsfrüherkennungs- und -registergesetz)
MV: Mecklenburg-Western Pomerania (Mecklenburg-Vorpommern)
OPS: Operation and procedure (Operationen- und Prozedurenschlüssel)
OS: Overall Survival
RCTs: Randomized Controlled Trials
RPpsm: Royston‒Parmar parametric survival model
RMST: Restricted Mean Survival Time
UICC: Union for International Cancer Control
